##### Brain function

A task-related fMRI activation sequence will be administered at PRE and F4 for a subgroup of participants (*N* = 54). This will measure activation while participants perform an associative memory encoding task. In this task, which was developed by CIMA-Q [32], participants are presented with a random sequence of 78 images and control stimuli (grey squares) for 3 s each. Each image appears within one of the four quadrants of the screen and participants are asked to remember the image and its position. Retrieval is tested outside the scanner after a 10-min delay where participants see series of 80 targets and 20 foils and are asked to indicate whether the image was presented and its position. An event-related model will allow analysis of activation as a function of whether the item and its position were correctly recognized (i.e., “correct item/correct position” versus “correct item/wrong position” and “incorrect item”).

##### Expectation measure

We will assess the expectations of participants regarding the training program to which they participated using a questionnaire adapted from prior studies [29, 68] administered at PRE and F4. The questionnaire consists of 10 questions using 0–6 answer scales. The expectation score (max = 60) will be compared between groups.

### Data storage and data transfer procedure

All the data collected will be included in the CCNA Longitudinal Online Research and Imaging System (LORIS) system [69] which will house the data from every COMPASS-ND participating institution. It will allow direct data entry from the two study sites into a single centralized system accessible by both teams. LORIS is a web-based database solution for neuroimaging and other research data that is physically located at McGill University in Montreal. Information and datasets are stored in the LORIS database under strict security provisions. Safeguards are in place to minimize the risk of a breach in the security of this database system resulting in the access of information. In the unlikely case of a security failure, research participants would be immediately notified by the site investigator. This procedure is described in the informed consent signed by the participants at study entry.

To ensure quality of data entry and error corrections, a double-entry procedure will be used. This procedure requires two different persons to enter the same set of data from the paper or computer files used during assessment. Any inconsistency is flagged by the system and the conflict will be resolved by confirming the correct data is entered into the system.

### Safety procedures

All data will be de-identified. Study participants will be assigned a unique anonymized study identification number that will be used to store their data. Brain images will be processed to remove any direct identifiers of an individual study participant. Information about study participants will be made publicly available to the extent permitted by the applicable laws and regulations. In CCNA publications, only group data will be reported. In cases where participant identification is required (e.g., when an incidental finding is uncovered on coded data), the recruiting site study investigator will be informed and be given access to the minimum identifying information required to associate the incidental finding to the participant identity and move it toward a resolution. For data stored locally at the training site, all documents will be anonymized and stored in a locked filing cabinet in a locked room, or on an encrypted and password protected computer, with access strictly restricted to the research team coordinators. Electronic files which contain names and contact information of participants will be encrypted and password protected and stored in a password protected desktop computer at the training site (IUGM research center and Baycrest). No identifying personal information will be disclosed in any resulting publication or presentation.

With the participants’ written consent, audio- or video-recordings will be collected during the evaluation or training sessions for quality control or training purposes. These files will be kept on an encrypted and password protected computer under the responsibility of the principal investigator, with access strictly restricted to the research team coordinators. These files will be kept for analysis until the end of the project and then will be deleted from the computer. No transcription will be done. With the participant’s consent, some of the files recorded during the intervention sessions could be used for teaching, research, or scientific conferences. In this case, these specific files will be kept for 25 years.

### Quality control and monitoring

The programs are manualized to ensure consistency between sites and between trainers. Activity leaders for the cognitive sessions of ENGAGE-MUSIC/SPANISH and for the ENGAGE-DISCOVERY program will have a professional background in occupational therapy and/or psychology and neuropsychology. They will receive 20 h of training and will be asked to complete mock trials of the training sessions. Two people will lead the programs (one person in each city), except for the music and Spanish activities that will be led by professional music and Spanish teachers since they require specific expertise. The music and Spanish teachers will receive a 10-h training program covering the leisure manuals and the memory strategies that will be used in their course. All intervention sessions will be videotaped or audio-recorded for quality control purposes. Monitoring will be done on random sections (covering 20% of the program) to ensure adherence to manuals.

Assessors who will collect data for clinical measures, outcomes, and moderating variables will be trained by the COMPASS-ND team and by the research coordinator of the research team. For COMPASS-ND testing, they will be required to obtain COMPASS-ND certification. This certification includes 40 h web-training (involving reading about the tests, watching demo videos, answering quizzes, and practicing task scoring from the demo videos), completion of a mock testing session which will be videotaped, and live observation (though a webcam) during the first evaluation for assessment of adherence to protocol. All testing sessions with participants will be audio-recorded and random portions will be monitored for protocol compliance.

The quality control for recruitment and evaluation is done by a senior research coordinator. The quality control for intervention integrity is ensured by two clinicians ([name]) with expertise in the content of the interventions.

Any potential change in the protocol (current version V2, December 2018) will be handled by the central coordinator who will be in charge of ensuring that the information is transmitted to the two sites and reported to the ethics committee in the form of an ethics amendment request.

The CCNA COMPASS-ND study is audited yearly by an independent external scientific review committee.

### Statistical analyses

#### Sample size

The trial will recruit 144 participants. The sample size was estimated from a power analysis with G*power based on pilot findings collected with the MEMO program [10, 12], using word recall and face-name associations tasks. The MEMO program is included as part of the formal training in this intervention in addition to stimulating leisure activities and attentional training. Therefore, it is reasonable to expect that the effect should be at least as large as the one observed when using MEMO alone. The pilot data indicated a medium effect size for the group-by-time interaction when examining face-name association and a large effect size when examining word recall (see Additional file 2: Appendix 2). It shows that the sample size would be sufficient to detect an interaction given a similar effect size considering the same attrition rate that we obtained in this prior study (18%). Half of the sample will be recruited in Montreal and the other half will be recruited in Toronto.

#### Analysis of efficacy and maintenance on primary and secondary outcomes

Descriptive statistics will be used for demographics and baseline characteristics, with means and standard deviations given. We will compare the intervention groups on these variables using one-way analysis of variance (ANOVA) for continuous variables and Chi-square analyses for discrete variables. The primary efficacy analysis will be done with a modified intention-to-treat approach retaining all participants and identifying the characteristics of participants withdrawing from follow-up as well as the causes for withdrawal. As proposed for preference trials, a first set of analyses will only use fully randomized participants. This will be followed by analyses of the comprehensive cohort which will include those in the preference arms.

The linear mixed model will be used to assess the efficacy of the intervention. The mixed linear model has many advantages over typical ANOVA; it handles correlated data and is robust to unbalanced design, hence allowing for the inclusion of all participants, including those missing at follow-up. Missing data will not be imputed as mixed models use all available data, including those from participants having incomplete follow-up. The fixed effects will be intervention (ENGAGE SPANISH/MUSIC versus ENGAGE DISCOVERY), time (PRE versus F4), and their interaction. A significant interaction is expected if the intervention is more beneficial than the control condition. When an interaction is found, we will look at whether there is a significant difference between PRE and F4 in each group and assess group differences on change scores at post-training ([PRE – F4]/|PRE|). Efficacy is supported if the F4 change score is larger in the intervention group than in the control group. All analyses will be adjusted for site and baseline performance.

A similar approach will be taken for most of our secondary objectives. A set of secondary objectives of the study is to assess the long-term maintenance of the effect of the training. This will use a mixed linear model to test long-term maintenance of intervention effects (PRE versus F24) on primary outcome, as well as separate models (with three levels of time: PRE, F4, and F24) on measures of attentional control, psychological health variables (anxiety/depression, apathy, quality of life, help seeking), everyday functioning measures (MMQ, AMQ, ADCS-ADL-PI, the Cognitive Activities Questionnaire, Memory Toolbox, and DAFS-R), and on the structural brain measures (hippocampal volume and cortical thickness). Because the Jessen questions about subjective complaint are dichotomous, Chi-square analyses will be used to compare the number of participants who have a memory complaint before and after the intervention as a function of condition. For exploratory purposes and to inform future interventions, the above analyses will be repeated comparing the music and Spanish arms. The *p* values will be presented before and after adjustment for multiple comparisons based on the Hochberg procedure. All statistical tests will be two-tailed and a *p* value of less than 0.05 will indicate statistical significance. All computations will be made with SPSS version 23.0 (SPSS Inc., Chicago, IL, USA).

Functional MRI data will be subjected to standard pre-processing steps using SPM8 (i.e., motion correction, slice timing correction, co-registration with anatomical T1 image, spatial normalization). First level (individual) analyses will involve general linear models with box-car responses, convolving the time course of the event-related response per condition with the canonical hemodynamic response function. Second level (group) analyses will treat participants as a random variable, with each contrast tested at *p* < 0.05 after whole-brain, family-wise error correction. A cluster threshold of 50 or more contiguous voxels will be applied.

Preliminary analyses of the descriptive characteristics and baseline performance will be done after full recruitment is completed. Analysis of efficacy will be done at the end of the 4-month follow-up and long-term analyses will be done at the end of the 24-month follow-up.

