### Objectives and hypotheses

The primary objective of this study is to assess whether the ENGAGE-MUSIC/SPANISH program leads to cognitive gains in episodic memory at the immediate follow-up assessment in older adults with a subjective memory complaint when compared with an active control condition. The secondary objectives of this study are: to assess whether these cognitive gains are maintained at the 24-month follow-up; to determine the effect of the program on attentional control, psychological health, activities of daily living, and brain structure and function as measured by magnetic resonance imaging (MRI); and to identify if the characteristics of participants modulate outcomes. Finally, the study will examine whether music and Spanish lessons produce different effects on the primary and secondary outcome measures.

It is expected that the ENGAGE-MUSIC/SPANISH training will show evidence of efficacy: persons enrolled in the ENGAGE-MUSIC/SPANISH training program will have larger gains in the memory composite measure following training than participants enrolled in the active control condition. Secondary hypotheses involve maintenance of training gains, and effects of training on attentional control, daily functioning, well-being, and brain structure and function. It is hypothesized that training effects on the memory composite will be maintained at the 24-month follow-up assessment. As the ENGAGE-MUSIC/SPANISH program includes a component of attention training, it is expected that measures of attentional control will improve. It is also expected that cognitive improvement will transfer to measures of activities of daily living (e.g., managing finances, medication, grocery shopping) and that it will increase indicators of psychological health. Also, the ENGAGE-MUSIC/SPANISH training will result in measurable effects on the brain as assessed by both structural (cortical thickness and regional grey matter volume) and task-related MRI activation, and that these changes will be correlated with improved cognition. Finally, we hypothesize that participant characteristics (sex, age, education) will modulate efficacy and transfer.

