#### Primary outcome measure

The primary outcome measure will be performance on a composite episodic memory score measured at PRE and F4. The composite score will be computed by averaging *z*-scores from the delayed recall of the Rey Auditory Verbal Learning Test (RAVLT) [51] and the delayed recall of the face-name association taken from the CIMA-Q study [32]. The RAVLT consists of learning a list of 15 unrelated words (list A) over five trials, followed by one-trial learning and recall of an interference list (list B). Free recall of list A is tested immediately after recalling list B, and again 20 min later for delayed recall. The score that will be converted into a *z*-score to compute the composite score is the number of words recalled in the delayed trial (maximum score = 15). In the face-name association task, participants learn nine pairs of face + first name associations. They are asked to recall the name associated with the faces and to recognize the pairs among distractors immediately after learning and following a 20-min delay. The score obtained which will be used in the composite score will be the number of names recalled in the delayed trial (maximum score = 9).

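### The change-score rule that follows the interaction test has its sign reversed for the memory composite, and it divides by a z-score baseline that has no meaningful zero

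*Protocol article*

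**What the plan says.** All of this is in the protocol article.

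- **Order of steps** (Analysis of efficacy and maintenance on primary and secondary outcomes). A linear mixed model with intervention, time (PRE, F4) and their interaction comes first. Then: "When an interaction is found, we will look at whether there is a significant difference between PRE and F4 in each group". The same sentence adds that the analysts will "assess group differences on change scores at post-training ([PRE – F4]/|PRE"|), so the score is (PRE – F4)/|PRE|.
- **Decision sentence** (same section). "Efficacy is supported if the F4 change score is larger in the intervention group than in the control group".
- **Scale of the primary outcome** (Primary outcome measure). "The composite score will be computed by averaging *z*-scores from the delayed recall of the Rey Auditory Verbal Learning Test (RAVLT") and from the face-name task. The components are "the number of words recalled in the delayed trial (maximum score = 15") and "the number of names recalled in the delayed trial (maximum score = 9"). No reference population for the z-scores is named.
- **Hypothesis** (Objectives and hypotheses). Participants in the intervention arm "will have larger gains in the memory composite measure following training than participants enrolled in the active control condition".
- **Reach.** The next paragraph of the analysis section extends a similar approach to most secondary objectives, and sets all tests as two-tailed at 0.05.

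**The concern.** There are two separate faults in one formula.

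**Sign.** Both components count correct recalls, so a gain means F4 above PRE and the score is negative. A bigger gain makes it more negative. A rule that asks for a larger score in the intervention arm is then met when that arm gains less or declines more.

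**Denominator.** Relative change needs a scale with a true zero. A z-score's zero is only the mean of whichever reference was used, so the same gain in recall gets a different score depending on how far the participant started from that mean.

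The interaction test is two-tailed and does not itself name a direction. The article gives that task to the change score. A beneficial interaction would therefore be followed by a pre-specified criterion that denies it, and repairing the criterion after seeing the data would be a post hoc change on the primary outcome.

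**Working it through.** The article gives no computed figure for the change score, so there is none to reproduce.

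**1. Sign (text only).** Score = (PRE – F4)/|PRE|. For a gain of 0.5:
- PRE = 0.5, F4 = 1.0: (0.5 – 1.0)/0.5 = –1.0
- PRE = –0.5, F4 = 0: (–0.5 – 0)/0.5 = –1.0

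Every improver scores below zero, whatever the baseline.

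**2. Denominator, same gain of 0.5.**
- PRE = 0.05 or –0.05: –0.5/0.05 = –10
- PRE = 0.01: –0.5/0.01 = –50

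**3. How many participants sit near zero.** Assume baseline-sample z-scores (mean 0), approximate normality and a correlation of 0.4 between the two components. Composite SD = √((1 + 0.4)/2) = 0.84, and P(|PRE| < 0.1) = 2Φ(0.1/0.84) – 1 ≈ 0.095. Component correlations of 0.3 to 0.7 give 0.099 to 0.086. If an external reference moves the baseline mean to 1, the share is about 5%; at 2 it is under 1%; at 3 it is practically nil.

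**4. Effect on the verdict.**

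Inputs from the article: 144 participants, 2:1 allocation, 18% attrition. 144 × 0.82 = 118 completers, or 79 and 39.

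Assumed inputs: true benefit 0.5 composite SD, PRE–F4 correlation 0.5 to 0.7, component correlation 0.4, baseline mean 0.

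Plain F4 – PRE: the SD of change is √(2(1 – ρ)) composite SDs, and the standard error factor is √(1/79 + 1/39) = 0.196.
- ρ = 0.5: standardised difference 0.5/1.00 = 0.50; 0.50/0.196 = 2.55; power about 72%
- ρ = 0.7: 0.5/0.775 = 0.645; 0.645/0.196 = 3.30; power about 90%

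Ratio as written, simulated over the same range (ranges cover repeated runs):

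| Result for the intervention arm | Share of trials |
|---|---|
| Mean ratio larger | about 14–19% |
| Mean ratio larger, among trials with a significant plain difference | about 13–14% |
| Significantly larger | about 0% |
| Significantly smaller (wrong verdict) | about 15–21% |

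**5. Separating the two faults.** These runs used a gain of 0.5 against 0.1 in composite units, component correlation 0.5 and ρ = 0.7.
- Baseline mean 0, sign reversed but |PRE| kept: right direction in 84% of trials, significant in only 16%, against 87% significant for the plain difference. Correcting the sign alone is not enough.
- Baseline mean 3, formula as written: no near-zero denominators, yet the intervention ratio is larger in only 3% of trials and significantly smaller in 63%. The sign fault does not depend on the z-score reference.

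**The case against.** The strongest reply is that the efficacy test is the mixed-model interaction. It is fitted to the composite itself, comes first, and does not use this formula. With two time points it is close to a test of F4 – PRE, so it should have roughly the power shown for the plain difference. That stands. A reader might infer that the primary test is invalid or that the trial could not detect a benefit; the article does not support this. What remains is that the sentence declaring efficacy supported is tied to the ratio.

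A second reply is that the near-zero denominator depends on how the z-scores are standardised, which the article does not state. That also stands: the share of participants affected is conditional, though the lack of a meaningful zero is not.

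A third is that an analyst would notice the sign, or would read larger as larger in magnitude. The text does not say magnitude, and that reading would count a greater decline as benefit.

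Finally, it is tempting to say that the rule points the wrong way for memory and the right way for the attention composite, which is built from reaction times and costs. This is only partly supported. The article does not say whether the attention z-scores are reversed, and it does not repeat the formula for secondary outcomes.

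**Conclusion.** The point holds, with different certainty for its two parts.

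- **Sign: certain from the text.** The literal rule contradicts a beneficial interaction on the primary outcome, and nothing elsewhere in the article repairs it.
- **Denominator: not meaningful in principle, with a conditional size.** The figure of about 9–10% of participants with |PRE| below 0.1 requires standardisation to the baseline sample.

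The simulated rates rest on the assumed benefit, correlations and baseline mean given above. Two stronger readings should be avoided. A working programme would not always fail the rule: by chance the intervention mean is still the larger in about 14–19% of trials. And the 15–21% of significant results on the ratio are not power, since almost every significant result on the ratio points the wrong way.

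Because the rule governs how the primary result is declared, it should be corrected before the 4-month efficacy analysis.

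**What to change.** 1. Delete (PRE – F4)/|PRE|.
2. Define change on the primary composite as F4 – PRE, with component z-scores at all visits standardised to the pooled PRE mean and SD.
3. State that efficacy is supported when the mixed-model between-arm contrast in F4 – PRE favours the intervention at the two-sided 0.05 level already set.
4. State the direction of benefit for each secondary outcome to which the same approach is applied.

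Cost: a small protocol amendment. Under Quality control and monitoring, changes go through the central coordinator and to the ethics committee as an amendment request. Data collection, visits and sample size are not affected.

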### Randomization and blinding procedure

The opportunity to exclude either music or Spanish training will be offered to all participants prior to randomization. Randomization will be done individually (i.e., one participant at a time as they enter the study) with random lists of binary numbers. Lists will be generated using the Random.org online software. Randomization will be controlled by a person from the Montreal site who is independent of the study. A first randomization will allocate participants to the intervention or control condition by matching the sequential list of participant identification codes with the list of random condition allocation. This will be done with a 2 to 1 ratio between intervention and control conditions. A second randomization will be used to allocate participants in the intervention condition to either Spanish or music training, using a 1 to 1 ratio for participants who did not exclude either of these two activities. Participants randomized in the intervention condition who excluded music or Spanish training will be placed in their preferred activity. Recruiting staff will contact (via telephone) the trial allocation office in charge of randomization once a participant has consented to participate and will be given the allocation. The allocation and sequence of allocation will be concealed from evaluators.

Evaluators who will be assessing the participants will be blinded to the hypotheses and to the group assignment of participants. Participants will be asked not to mention their group assignment to evaluators. Any breach of this group assignment blinding by participants will be noted, but since evaluators will be blinded from the hypotheses this should have minimal effect on integrity. Activity leaders will not be blinded to the study hypotheses. Although participants will know that they are in the Spanish, music, or documentary discussion group, they will not be informed of the study hypotheses, i.e., participants assigned to ENGAGE-DISCOVERY will be unaware that it is an active control condition. To keep participants blinded from the hypotheses and reduce the likelihood that the expectations of participants bias the data [29], close attention will be paid to ensure that the content of the intervention and the wording of recruitment documents and consent forms do not convey the expectations that one condition is inferior in terms of its effect on the brain and cognition.

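### The efficacy model lists no site-by-time term, so the promised adjustment for site and baseline does not act on the intervention-by-time test; the cost is some precision, not validity

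*Protocol article*

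**What the plan says.** All of this is in the protocol article. The section on analysis of efficacy and maintenance specifies the linear mixed model: "The fixed effects will be intervention (ENGAGE SPANISH/MUSIC versus ENGAGE DISCOVERY), time (PRE versus F4), and their interaction". The interaction is the efficacy test. Only when it is found does the plan go on to compare PRE with F4 within each group, and to compare relative change scores between groups. The paragraph ends: "All analyses will be adjusted for site and baseline performance". It does not say whether site or baseline is crossed with time. On missing data: "Missing data will not be imputed as mixed models use all available data, including those from participants having incomplete follow-up".

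Three other sections bear on site. The sample size section plans 144 participants, half in each city, with 18% attrition. Quality control and monitoring says: "Two people will lead the programs (one person in each city", with music and Spanish taught by specialist teachers. The randomization section describes a 2:1 allocation made by "matching the sequential list of participant identification codes with the list of random condition allocation". It mentions no site strata.

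**The concern.** The efficacy test is about gain from PRE to F4. A site term that is constant over time corrects for sites that differ in level. It does nothing about sites that differ in gain. The same holds for baseline performance entered as a constant covariate in a model where PRE is itself one of the two outcomes.

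A difference in gain between sites is conceivable here, because each city has its own programme leader, and language and assessors may differ as well. A reader of the plan would take the primary test to be protected against such a difference. With the terms as listed, it is not. What is at stake is the precision that a working adjustment would give, and agreement between what the plan promises and what its model does.

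**Working it through.** **Inputs from the article.** N = 144, 72 per site; 2:1 allocation, so 96:48; attrition 18%, so 144 × 0.82 ≈ 118 completers, about 79:39; two-sided alpha 0.05.

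**Inputs assumed.** The site difference in gain, g, is not given. I use 0.2, 0.3 and 0.5 SD of change. The effect size d = 0.5 for the power figures is also an assumption.

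**The plan's own figure.** N = 144 cannot be reproduced, because the numeric effect size and target power are not in the text shown. A repeated-measures interaction calculation, inflated for 18% attrition, gives 42 to 130 for f = 0.25 and 110 to 355 for f = 0.15 (power 80% to 95%, PRE–F4 correlation 0 to 0.5). So 144 is plausible, and this point does not dispute it.

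**Step 1: the cancellation.** Let T be the arm and S the site.

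- PRE = μ + αT + σS + e₁
- F4 = μ + τ + (α + δ)T + σS + e₂
- F4 − PRE = τ + δT + (e₂ − e₁)

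The site coefficient σ has gone, and δ is the tested interaction. Replace S by the baseline score and the same algebra removes it from the estimate of δ. Only a site-by-time term, γS × time, would survive the subtraction.

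**Step 2: numerical check for site.** One simulated trial (95:49, compound-symmetry covariance held fixed), interaction estimate (standard error):

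| Site gap in gain | No site term | Site main effect | Site and site-by-time |
|---|---|---|---|
| 0.3 | 0.46758 (0.15731) | 0.46758 (0.15731) | 0.45371 (0.15747) |
| 0.5 | 0.41552 (0.15731) | 0.41552 (0.15731) | 0.40985 (0.15747) |
| 1.0 | 0.45155 (0.15731) | 0.45155 (0.15731) | 0.39483 (0.15747) |

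Under an unstructured covariance the first two columns again agree to five decimals. With 18% of F4 missing, the site main effect moved the estimates by 0.0015 to 0.0115 and the standard errors hardly at all. Because the covariance is held fixed, this table shows the cancellation but not the gain in precision.

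In a separate simulated mixed-model fit, the estimate was 0.250787 (SE 0.15921) both without site and with a site main effect. It was 0.263563 (SE 0.156164) with site-by-time. The variance ratio is (0.156164/0.15921)² ≈ 0.96, about 4% lower.

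**Step 3: the size of the loss.** With half the sample at each site, an unmodelled gap g adds g² × ½ × ½ = g²/4 to a change variance of 1. Power uses SE = √(1 + g²/4) × √(1/79 + 1/39), where the second factor is 0.1957. With g = 0, 0.5/0.1957 = 2.555 and Φ(2.555 − 1.96) = 72.4%.

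| g (SD of change) | Variance factor | Power at d = 0.5 |
|---|---|---|
| 0 | 1.000 | 72.4% |
| 0.2 | 1.010 | 72.0% |
| 0.3 | 1.0225 | 71.5% |
| 0.5 | 1.0625 | 69.8% |

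**Step 4: validity.** Over 20,000 simulated trials of 118 with no intervention effect, type I error without site was 0.050 at g = 0.2 and 0.052 at g = 0.5. With site it was 0.051 and 0.050. Over 200,000 simulated unstratified lists, the shift in the estimate averaged zero.

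**The case against.** The strongest reply is that the article does not fix the form of the site term. It is a condensed document, and whether site is crossed with time is a detail that a fuller analysis plan may settle. That stands, and it limits the point to the plain reading. It does not remove the point: the article does list its fixed effects, lists no site-by-time term, and promises an adjustment that those terms cannot deliver for the stated test.

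Second, the adjustment also covers the change-score comparison, where a site covariate acts directly on gain. That is correct. But this comparison follows only a significant interaction, so it cannot help the primary test.

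Third, no passage reports a site gap in gain, and the article describes measures against one: manualized programmes, 20 h of leader training, monitoring of 20% of the programme and certification of assessors. This stands too. It is why g is an assumption and why the lower end of the range may be nearer the truth.

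Three stronger readings are tempting, and the documents do not support them:

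- **That site differences bias the result.** Nothing in the allocation procedure makes arm depend on site, so the unadjusted interaction is unbiased. With one unstratified list, the arms' site shares would differ by chance with SD √(0.25/96 + 0.25/48) = 0.088. A gap of 0.3 to 0.5 SD would then shift a single estimate by up to about 0.05 to 0.09 SD (95% limit). That shift has mean zero and is the same variance as in the table of losses, already carried by the standard error.
- **That allocation is not split by site.** The article says: "Randomization will be done individually (i.e., one participant at a time as they enter the study) with random lists of binary numbers". It describes no site strata, but it speaks of lists in the plural and does not rule strata out.
- **That screening memory scores crossed with time would add much.** The correlation of a covariate with change is (ρ₂ − ρ₁)/√(2(1 − r)), with equal variances, where ρ₁ and ρ₂ are its correlations with PRE and F4 and r is the PRE–F4 correlation. At assumed ρ₁ = ρ₂ = 0.5 it is zero. At 0.5 and 0.55 with r = 0.5 to 0.7 it is 0.05 to 0.065, which removes about 0.3% to 0.4% of the variance of change.

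**Conclusion.** The point holds in a limited form. On the plain reading, the adjustment for site and baseline does not act on the primary intervention-by-time test. For site, the cancellation is exact in estimate and standard error with complete pairs, and nearly so with 18% of F4 missing. For baseline, the estimate is unaffected by the same algebra.

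The consequence is lost precision only: 1.0% to 6.3% of variance and 0.4 to 2.6 percentage points of power, if the sites differ in gain by 0.2 to 0.5 SD of change and d = 0.5. Bias is zero and type I error stays at about 5%. The finding rests on site being a main effect, which the article implies but does not state, and its size rests on a site gap that the article does not report. It is worth correcting because a better model is available from data already collected.

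**What to change.** State the form of the adjustment in the efficacy model, in one of two ways:

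- Add site-by-time to the mixed model. This makes the site adjustment act on gain and keeps every participant in the model, as the plan intends.
- Better, analyse F4 with PRE and site as covariates. This makes both promised adjustments work. With equal variances σ² and PRE–F4 correlation r, the residual variance is σ²(1 − r²) against 2σ²(1 − r) for change. The ratio is (1 + r)/2, which is below 1 for any r below 1.

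Either costs one line of model wording, no new data and about one degree of freedom. In the second form, participants without F4 do not contribute, so the statement that all participants are retained would need matching wording. It would also help to state whether allocation is stratified by site.
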